|                                              | 
therapy prior to screening visit can skip the washout period if they meet the subject qualification criteria and be administered with investigational product.
 
Subjects who are qualified as the result of qualification examination results according to the selection criteria after completing the washout period are randomly assigned at the ratio of 1:1 to control group or test group. Randomly assigned subjects are medicated with study drug or control drug for 28 days and they are evaluated in terms of effectiveness and safety by visiting the testing institution on day 14 and 28 after medication.
                                                                                                                           |                                              |                |               |                |                                              |                                      |               |         |                                            |               |                                              |                                              |
| Investigational products                     | 

• Study drug: Pelubi CR tablet(Pelubiprofen 45mg)

• Control drug : Airtal tablet(Aceclofenac 100mg)

• Rescue drug : Tylenol ER tablet 650mg(Acetaminophen)

                                                                                                                                                                                                                                                                                                                                                                                                                                                                                                                                     |                                              |                |               |                |                                              |                                      |               |         |                                            |               |                                              |                                              |

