| Confirmation of pain reliever administration stoppage        |                             | X                     |         |         |
| Random assignment                                            |                             | X                     |         |         |
| 100mm Pain VAS assessment                                    | X                           | X                     | X       | X       |
| K-WOMAC assessment                                           |                             | X                     | X       | X       |
| Patient Global Assessment                                    |                             |                       | X       | X       |
| Adverse events                                               |                             |                       | X       | X       |
| Confirmation of change in co-administered drugs  |                             |                       | X       | X       |
| Prescription of investigational product                      |                             | X                     | X       |         |
| Rescue drug prescription and distribution of rescue drug log | X                           | X                     | X       |         |
| Survey on frequency of rescue drug usage                     |                             | X                     | X       | X       |

- 
- 1 For subjects administered and treated with non-steroid anti-inflammatory pain reliever, osteoarthritis supplements, physical therapy, and oriental therapy(Acupuncture, cupping, moxibustion) within 2 weeks prior to screening must stop such administration and treatment for 14 days for a washout period and subjects without administration and treatment within the past 2 weeks can be administered with investigational products without having a washout period.
  - 3 It can be substituted with test results within 3 months from screening date.
  - 4 It can be substituted with test results within 4 weeks from screening date.

|                      |                                                                                                                                                                                     |
|----------------------|-------------------------------------------------------------------------------------------------------------------------------------------------------------------------------------|

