### 3.2.2 Basis of Calculation

The primary purpose of this clinical trial is to prove noninferiority of test group compared to control group within clinical tolerance limit regarding the effect of pain relief evaluated by 100mm Pain VAS compared to baseline after administering the study drug or control drug for 28 days.

This clinical trial inferred from the study results of aceclofenac tablet(Aceclofenac vs paracetamol in the management of symptomatic osteoarthritis of the knee : a double-blind 6-week randomized controlled trial. Osteoarthritis and Cartilage 2007;15(8):900-908) in order to calculate the number of subjects necessary to prove noninferiority for this clinical trial. As a result of clinical trial conducted on patients with osteoarthritis of the knee for

aceclofenac tablet in terms of change in 100mm Pain VAS and standard deviation was  $-18.34 \pm 24.86$ mm and the combined standard deviation for this clinical trial based on this result was established as  $\pm 24.86$ mm and clinical tolerance was established as -15mm which came from references.

The following assumptions and hypotheses were established in order to prove noninferiority within clinical tolerance limit in terms of change in test group compared to that of control group.

- (1) Level of significance,  $\alpha=0.025$  (One-sided test)
- (2) Power of the test,  $1-\beta=0.975$
- (3) Test group to control group ratio,  $\lambda=1$
- (4) Standard deviation between test and control groups,  $\sigma_t=\sigma_c=24.86$ m
- (5) Clinical tolerance for noninferiority test,  $\delta=-15$ mm
- (6) Trace loss rate is assumed to be 10% ( $r=0.10$ )

Hypotheses of the noninferiority test for verification are as below.

$$H_0 : \mu_t - \mu_c \geq \delta$$

$$H_1 : \mu_t - \mu_c < \delta$$

The test variables required for the clinical trial are as below assuming (1)~(5) are true.

$$n_t = \frac{(\sigma_t^2 + \sigma_c^2)(Z_{1-\alpha} + Z_{1-\beta})^2}{\delta^2}$$

Number of subjects required per group according to equation above is 85 and it becomes 95 people per group considering the dropout rate of 10%.

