#### **4.2.2 Visit 2(Random Assignment and Administration of Investigational product, Day 1)**

This visit takes place after washout period(3~14 days) for subjects administered pain relievers and such and the evaluations for this visit are as below.

- 1) Check for changes in medical/medication history compared to previous visit.
- 2) Check for washout period for pain reliever, etc.
- 3) Measure vital signs and weight and conduct physical examination.
- 4) Evaluate 100mm Pain VAS.
- 5) Combine all examination and evaluation results including clinical lab results up until this point and perform final evaluations whether qualified subjects according to inclusion/exclusion criteria have been selected.
- 6) Assign assignment number through random assignment.
- 7) Evaluate K-WOMAC.
- 8) Train on administration method and distribute investigational products.
- 9) Recover residual clinical trials from the subject and record residual quantity.
- 10) Distribute new rescue drug.
- 11) Train on rescue drug log writing and distribute new rescue drug log.
- 12) Schedule next visit.

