### **7.2.3 Demographic Data and Baseline Data Analysis**

Mean, standard deviation, minimum and maximum values will be calculated for continues data in order to verify whether there is statistical difference between test group and control group regarding demographic and health statuses and comparison between the groups shall be performed through the t-test. Frequency between groups will be calculated and analyzed through the chi-square test or the Fisher's exact test in order to compare groups for categorical data.

Difference between groups regarding baseline observation values including demographic data of subjects will be observed in order to determine the pure treatment effect between test group and control group. Difference in demographic data or baseline observation values between test group and control group will result in such difference being considered as a disturbance factor should it be determined as being relevant to the effectiveness evaluation variables which is to be processed through subgroup analysis or being included in the effectiveness analysis as a covariate.

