#### **7.2.4.1 Primary Effectiveness Analysis**

- Change in 100mm Pain VAS on 28th day compared to baseline

Calculate the upper limit(97.5% one-sided confidence interval) for 95% two-sided confidence interval for the difference in change of 100mm Pain VAS on the 28th day compared to baseline of test and control groups(Average change in test group - Average change in control group). If the upper limit of the confidence interval is below 15mm, then it shall be determined that the test group is not inferior compared to the control group. For this, configure the change in 100mm Pain VAS as dependent variable with the administration group as the random factor, and the baseline 100mm Pain VAS as the covariate to perform the covariance analysis. Suggest the calibrated average for the change in 100mm Pain VAS for each administration group based on this analysis and suggest the difference in calibrated means between the two group and its 95% confidence interval.

Additionally, mean, standard deviation, minimum and maximum values shall be suggested for the amount of 100mm Pain VAS measured at each visit for the test group and the control group and the change in 100mm Pain VAS on the 28th day compared to baseline.

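### Optional gain: prespecify washout status, known before randomisation, as a covariate in the primary ANCOVA instead of leaving it to the imbalance-triggered rule in 7.2.3

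*Protocol*

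**What the plan says.** **Two entry routes.** Under the Overview (Method) and 3.1 Design, subjects recently treated with anti-inflammatory or narcotic analgesics, osteoarthritis supplements, physical therapy or oriental therapy stop these before dosing. Those with no restricted drug or "therapy prior to screening visit can skip the washout period if they meet the subject qualification criteria and be administered with investigational product".

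**Known before assignment.** Medication history is taken at Visit 1. At Visit 2 (4.2.2) step 2 is "Check for washout period for pain reliever, etc", ahead of random assignment at step 6. The Clinical Trial Schedule has a matching Visit 2 row, "Confirmation of pain reliever administration stoppage". Section 3.4 describes one sequential random list, with no stratification by washout status.

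**Primary model.** Section 7.2.4.1 takes treatment group and "the baseline 100mm Pain VAS as the covariate to perform the covariance analysis". Non-inferiority is concluded "If the upper limit of the confidence interval is below 15mm". Section 7.2.4.2 applies the same method to Day 14 VAS.

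**Other covariates.** Section 7.2.3 handles a baseline variable that differs between arms and is judged relevant to effectiveness by subgroup analysis or by its "being included in the effectiveness analysis as a covariate". It does not name washout status.

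**The concern.** Baseline VAS records how much pain a subject has, not how it arose. For a subject just taken off an effective analgesic, the Visit 2 score may include pain that returned on withdrawal. For a subject who skipped the washout, it is the usual untreated level. At the same score, the two may change by different amounts over 28 days. If so, washout status predicts the outcome beyond baseline VAS, and it is already collected.

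The verdict rests on one confidence limit. Leaving out a real predictor makes that limit slightly less precise than it could be at no cost. The fallback in 7.2.3 is also the weaker route. It lets the primary model depend on imbalance seen in the data and on a judgement of relevance, and it does not say whether a subgroup analysis or a covariate would follow.

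**Working it through.** **Inputs from 3.2.2 and 7.2.4.1.** One-sided alpha 0.025; power 0.975; 1:1 allocation; margin 15 mm; 10% dropout. The SD of VAS change is taken from the aceclofenac study, where the "combined standard deviation for this clinical trial based on this result was established as" 24.86 mm. The formula divides by the squared margin alone, so the true difference is taken as 0.

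**Inputs assumed, because the documents do not give them.** Washed-out share p of 30-70%; gap g in 28-day change at equal baseline VAS of 5, 10 or 15 mm; correlation rho of baseline with Day 28 VAS of 0.3-0.5, with equal variances. Washout status is taken as uncorrelated with baseline VAS; a correlation would make the gain smaller. Baseline is taken as the Visit 2 score.

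**1. The plan's own figure.** n = 2 × 24.86² × (1.96 + 1.96)² / 15² = 84.4, so 85 per arm; 85/0.9 = 94.4, so 95. Both stated figures reproduce. At 85 per arm, SE = 24.86 × √(2/85) = 3.81 mm and power = Φ(15/3.81 − 1.96) = 97.6%.

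**2. Residual SD once baseline VAS is in the model.** Residual variance = 24.86² × (1 + rho)/2.
- rho 0.5: 463.5, SD 21.53 mm, SE 3.30 mm, 95% half-width 6.47 mm, power 99.5%.
- rho 0.3: 401.7, SD 20.04 mm, SE 3.07 mm, half-width 6.03 mm, power 99.8%.

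**3. Gain from adding washout status.** Share of residual variance explained = p(1 − p)g² / residual variance; relative narrowing = 1 − √(1 − share). Over p = 30-70% and both values of rho:

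| Gap g | Variance explained | CI narrows by | Half-width falls by |
|---|---|---|---|
| 5 mm | 1.1-1.6% | 0.6-0.8% | 0.04-0.05 mm |
| 10 mm | 4.5-6.2% | 2.3-3.2% | 0.15-0.19 mm |
| 15 mm | 10.2-14.0% | 5.2-7.3% | 0.34-0.44 mm |

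Worked corner (g = 15, p = 0.5, rho = 0.3): 0.25 × 225 / 401.7 = 14.0%; 1 − √0.86 = 7.3%; 7.3% of 6.03 mm = 0.44 mm.

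If baseline VAS explains nothing, the SD stays at 24.86 mm. With p = 50%, the half-width then falls from 7.47 mm to 7.44, 7.32 or 7.13 mm for the three gaps.

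**4. Effect on power.** With a true difference of 0, the largest gap and p = 0.5, power moves from 99.5% to 99.8% (rho 0.5) or from 99.8% to 99.95% (rho 0.3). If the test drug were truly worse, there is more to gain. With SD 24.86 mm and a covariate explaining about 4% of the variance (a 10 mm gap at p = 0.5), power moves from 88.2% to 89.5% at a true difference of 3 mm, and from 74.6% to 76.3% at 5 mm.

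**5. Chance imbalance is the same loss.** The SD of the between-arm difference in washed-out share is √(p(1 − p) × 2/85) = 7.0-7.7 percentage points, or 0.70-0.77 mm in the estimate at a 10 mm gap. At p = 0.5 and rho 0.5, (0.77/3.30)² is about 5.4%, the variance share already counted in step 3. It must not be added on top.

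**6. Cost if there is no gap.** One of 167 residual degrees of freedom: √(167/166) = 1.003, about 0.3% on the standard error.

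**The case against.** The strongest reply is that nothing here is wrong. ANCOVA on treatment and baseline VAS is valid, other baseline variables such as site and radiographic stage are also left out, and the non-inferiority decision already has 97.6% power or more under the plan's assumptions. All of that stands, and it is why the point is only optional. It does not show that adding the term would be a mistake, since the cost is negligible and the variable is one that the design itself creates.

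The mechanism is also uncertain. Washout applies equally to subjects who stopped only supplements, physical therapy or oriental therapy, and they do not resume a lost analgesic when dosing starts. Every subject must reach 40 mm at Visit 2, after any washout, so part of any withdrawal pain already sits in a Visit 2 baseline. A yes/no indicator also mixes different prior treatments and washout lengths. These points stand and argue for the lower part of the assumed range.

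A reader might infer that the plan discards washout status altogether. It does not: 7.2.3 offers a route for a variable that differs between arms and is judged relevant. The narrower criticism is that this route waits for observed imbalance and leaves the form of handling open.

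**Conclusion.** The point holds as a minor, nearly free efficiency improvement. Washout status is fixed before randomisation, the primary model omits it, and prespecifying it is better than admitting it after an imbalance is seen. Under assumed gaps of 5-15 mm the interval narrows by roughly 0.5-7%, at most about 0.44 mm on the half-width against a 15 mm margin.

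Everything about size rests on assumed values for the washed-out share, the gap and the baseline correlation. That washout status predicts change beyond baseline VAS is plausible but not documented.

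A reader might infer that the treatment comparison is biased or the trial underpowered. Neither follows: randomisation protects the comparison on average, and the stated 85 and 95 per arm reproduce with the stated power.

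**What to change.** In 7.2.4.1, and so for Day 14 VAS in 7.2.4.2, name washout status at Visit 2 (washed out or skipped) as a fixed covariate next to baseline VAS, whatever the observed balance. State that it is therefore outside the conditional rule in 7.2.3.

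Before that, reconcile how the washout is described, or the status cannot be coded consistently. The Overview and 3.1 count treatment in the 2 weeks before administration and give a stop of 3 to 14 days, and 4.2.1 and 4.2.2 repeat the 3 to 14 days. Footnote 1 of the Clinical Trial Schedule counts from screening and gives 14 days. Which description applies is for the sponsor to settle.

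The cost is one sentence in 7.2.4.1, the reconciliation, and one degree of freedom. No new data, visits or subjects are needed.

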## ▣ Overview of Clinical Trial Plan

|                           |                                                                                                                                                                                                                                                                                                                                                                                                                                                                                                                                                                                                                                                                                                                                                                                                                                                                                                                                                                                                                                                                                                                                                                                                                                                                                                                                                                                                                                                                                                                                                                                                                                                                              |
|---------------------------|------------------------------------------------------------------------------------------------------------------------------------------------------------------------------------------------------------------------------------------------------------------------------------------------------------------------------------------------------------------------------------------------------------------------------------------------------------------------------------------------------------------------------------------------------------------------------------------------------------------------------------------------------------------------------------------------------------------------------------------------------------------------------------------------------------------------------------------------------------------------------------------------------------------------------------------------------------------------------------------------------------------------------------------------------------------------------------------------------------------------------------------------------------------------------------------------------------------------------------------------------------------------------------------------------------------------------------------------------------------------------------------------------------------------------------------------------------------------------------------------------------------------------------------------------------------------------------------------------------------------------------------------------------------------------|
| Inclusion Criteria | 

1. Male and female patients between age 35~80

2. Patients diagnosed with osteoarthritis of the knee according to ACR diagnosis criteria with Kellgran & Lawrence stage I~III diagnosis on x-ray imaging

3. Patients evaluated with osteoarthritis to be stable for 3 months prior to clinical trial by clinical physician

4. Patient with at least 40mm on 100mm Pain VAS scale at visit 2

5. Patients who voluntarily gave consent in written form to participate in this clinical trial

                                                                                                                                                                                                                                                                                                                                                                                                                                                                                                                                                                                                                                                                                                                                                                                                                                                                                                                                                                                                                                                                                                |
| Exclusion Criteria | 

1. Patient with secondary osteoarthritis

2. Patient suffering from disease that may affect the effectiveness assessment such as bursitis, tenosynovitis, fibromyalgia syndrome, rheumathritis, and other inflammatory joint disease

3. Subject with confirmed with an ulcer or stomach disease through gastroscop

4. Patient with history of invasive knee joint operation, knee joint injury, arthroscopic joint operation within 12 months prior to screening visit or patient scheduled operation during clinical trial period

5. Patient with history of artificial joint surgery for knee joint

6. Patient with malignant tumor(However, patient without remission within 5 years after completion of treatment can be registered)

7. Patient with regular administration of psychoactive drug or narcotic analgesic which may affect sense of pain for at least 3 months

8. Subject administered with glenoid cavity injection or systemic injection(Oral administration or absorption of corticosteroid for 1 day exceeding 1500<math>\mu</math>g) of steroid within 3 months prior to screening visit

9. Subject with hyaluronic acid injection for knee joint within 2 months prior to screening visit

10. Subject with intercurrent disease or medicated with co-administered drugs that are prohibits prescription of non-steroid anti-inflammatory pain reliever

11. Patient with history of asthma, hives, and allergic reaction against aspirin or other non-steroid anti-inflammatory pain reliever(COX-2 inhibitor included)

 |

